## Abstract

Background/Objectives: Correction of decreased diversity of the gut microbiome, which is characteristic of menopause, by supplementation with a synbiotic may attenuate or prevent dysbiosis processes and preserve bone mass. We describe the rationale and design of the OsteoPreP trial aimed at evaluating the effects of 12 months of supplementation with a synbiotic on bone and metabolic health in postmenopausal Caucasian women. Methods: This is a randomized, double-blinded, placebo-controlled trial among 160 Caucasian, postmenopausal women with no current diagnosis of osteoporosis or supplementation with pro- or prebiotics, and no medical treatment affecting bone turnover. Dual-energy X-ray absorptiometry scans will be conducted at screening to confirm absence of osteoporosis. The primary outcome is the relative change (%) in total bone mineral density of the distal tibia at 12 months post-treatment between the active and placebo groups, as determined via high-resolution peripheral quantitative computed tomography. Secondary outcomes are the effects on immune system modulation and cognition, gut microbiota composition, and musculoskeletal and metabolic functions, with particular emphasis on blood glucose regulation. Conclusions: The trial will inform on the efficacy and safety of a synbiotic containing both aerobic and anerobic bacterial strains and a prebiotic fiber on reduction in bone loss and on indices of blood glucose regulation. This trial may pave the way for an exciting field of translational research and be the underpinnings of the prevention strategy of osteoporosis and the management of metabolic dysfunction in postmenopausal women. The trial is registered with clinicaltrials.gov (NCT05348694).

## 1. Introduction

Osteoporosis, a silent, chronic, and multifactorial disorder, is the most common bone disease in humans and is characterized by loss of bone mineral density (BMD) and bone microarchitecture, resulting in decreased bone strength and greater risk of fracture [1]. Despite effective medications that substantially increase BMD and decrease fracture risk, only 30% of those at highest risk are receiving specific osteoporosis treatments in Australia [2]. Fractures of the distal forearm, vertebrae, and hip are the most serious consequences of osteoporosis [3,4]. Hip fractures are linked to an increased risk of mortality and loss of independence, whereas vertebral fractures are linked to significant long-term disability related to pain and kyphosis, leading to increased morbidity and mortality [4,5,6].

The prevalence of osteoporosis and osteoporotic fractures is influenced by various factors, including age, sex, menopausal status, race, and ethnicity. Compared with men, women over 50 years old have a fourfold greater rate of osteoporosis and a twofold greater rate of osteopenia [7]. Osteoporosis affects 200 million women worldwide, with Caucasian and Asian women being more susceptible to osteoporosis than black women [8,9]. This is due to variations in BMD across different racial and ethnic groups [10,11,12]. Osteoporotic fractures affect approximately 1 in 2 women and 1 in 5 men over the age of 50 years [13]. The highest fracture rates are reported among white women, whereas the lowest rates are reported in black women and are approximately 50% lower than those stated in white women [14].

Pharmacological treatments for osteoporosis have been indicated to reduce the risk of fractures by 20–70%, depending on fracture type, in controlled settings but have also proven costly and have been associated with adverse side effects, impacting treatment rates and medication adherence [15,16,17,18,19]. Previous studies in postmenopausal women reported that probiotics increase calcium absorption and 25-hydroxyvitamin D levels and decrease bone loss [20]. Additionally, beneficial effects on glucose regulation in trials investigating the effects of a probiotic or synbiotic (a mixture of probiotics and a prebiotic) intervention in postmenopausal women ranging from 6–12 weeks, including adults diagnosed with type 2 diabetes mellitus (T2DM), have been reported [21,22,23,24]. However, the magnitude of effect reported by these studies was small, perhaps owing to the short duration of these interventions, making it difficult to interpret how clinically meaningful these findings are.

The risk of osteoporosis in women increases in menopause due to a decrease in estrogen levels, and estrogen-independent mechanisms, including secondary hyperparathyroidism, chronic inflammation, and senility, can add to the development of osteoporosis [25,26,27,28,29]. Moreover, decreased diversity of the gut microbiome in menopause, known as dysbiosis, has been linked to metabolic syndrome, as well as behavioral and physiological deficits (Figure 1) [30,31,32,33]. Metabolic syndrome is a multiplex modifiable risk factor involving several health outcomes, including T2DM, which is normally associated with high body mass index, that share common biological and societal pathways [34,35,36,37,38,39]. T2DM is a worldwide disease affecting 462 million people, and with over 1 million deaths per year attributed to diabetes alone, it is the ninth leading cause of mortality [40]. T2DM cases are equally distributed amongst the genders, with the rate of the disease peaking at about 55 years of age.

The gut microbiota (GM) plays an important role in the maturation of the immune system, and both the GM and the immune system can regulate bone health [21,27,31,32,41,42], and varies with race, sex and ethnicity [43,44,45,46]. Postmenopausal women with a diagnosis of osteoporosis have also been reported to have a significantly different GM composition and diversity than those with normal bone mass with the genus *Prevotella histicola* being more prevalent in those with normal bone mass, suggesting its protective effects on bone health [47]. Probiotics, more specifically the regulatory role of short chain fatty acids (SCFAs) has been linked to maintaining an equilibrium in the GM by ensuring bone health is controlled by the immune system, and the potential of probiotic and prebiotic supplementation to stimulate SCFA production has been reported [48,49]. The SCFA butyrate (C4) has been identified as a major regulator of osteoclast metabolism and bone homeostasis by promoting the expansion of T regulatory (Treg) cells [50,51]. GM, through the production of SCFAs, has also been demonstrated to play important roles in regulating physiological functions, including blood glucose regulation, inflammation, brain function and behavior [32,52,53,54]. For example, it has been suggested that SCFAs generated from the gut microbiota regulate the number and function of regulatory T cells in the colon, thereby influencing the development of inflammation and associated diseases such as hypertension [55].

There is increasing evidence for an association of dysbiosis, or an imbalance in the gut microbiota, with psychiatric and cognitive dysfunction, suggesting the gut-brain axis is critical for the management of these conditions [56,57,58,59]. Gut microbiota, through the production of important neurotransmitters, has been demonstrated to play important roles in modulating the activity of the brain through immune pathways, which directly or indirectly guides social behavior [54,60,61]. As neuroinflammation is critically linked to indices of cognitive decline, investigating the potential benefits of increasing SCFAs could be particularly beneficial for the aging population.

Given the critical role of probiotics in several processes central to osteoporosis prevention, a unique opportunity exists to examine the safety and efficacy of this relatively inexpensive, readily available, oral dietary supplement in a clinical trial focused on preventing osteoporosis. The trial intervention is a formulation of five probiotic strains important for the production of SCFA butyrate, which have previously been found to be beneficial to bone and metabolic health and neurodevelopmental disorders [62,63,64,65,66,67]. Additionally, the intervention contains a prebiotic, inulin, known to promote the growth of beneficial microbes and/or promote beneficial changes in the activity of the microbiome [68]. To our knowledge, this is the first randomized controlled trial to administer a mix of all five probiotic strains and a prebiotic in a supplement formulation (Pendulum WBF-038) to human subjects with a risk of developing osteoporosis, over a 12-month treatment period. If supplementation with the trial synbiotic is beneficial for bone health, cardiometabolic health, muscle health, and cognition, the results of this trial could translate into significant improvements in the prevention of osteoporosis and related musculoskeletal and metabolic conditions, such as T2DM [69].

## 2. Materials and Methods

### 2.1. Trail Design

The trial is a randomized, double-blinded, placebo-controlled trial. Participants will be assessed at baseline (T0) upon recruitment and subsequently at five follow-up visits. The trial will be conducted in three, phases as summarized in Figure 2 and described in detail in Supplementary File S1.

Dual-energy X-ray absorptiometry (DXA) scans will be conducted on participants at screening. Following this, participants will be assigned randomly to either a synbiotic supplement or a matching oral placebo arm. The efficacy of the supplement will be established by comparing data collected after 12 months of treatment with those collected at T0. The study outcomes are illustrated in Figure 3. Only Caucasian women will be recruited in this trial owing to significant differences in BMD and bone remodeling between ethnicities and races.

The trial will be advertised on social media platforms, relevant public locations, and newspapers, and through assisted mail out of trial information conducted by a government agency to community-dwelling women aged 40–65 years residing in the inner suburbs of Melbourne, Victoria, Australia.

### 2.2. Participants and Recruitment Process

One hundred and sixty 40–65-year-old postmenopausal women will be recruited. Women interested in the trial will complete an online prescreening questionnaire, as advertised in the trial brochure. Further screening for eligibility will be conducted by trained research staff during telephone interviews. During this call, trial procedures and consent forms, including trial aims, requirements, participants’ right to withdraw, and any potential risks involved, will also be discussed. Eligible participants will be enrolled in the trial provided that no exclusion criteria are met at the time of screening, including the presence of osteoporosis, high blood pressure (BP), and diabetes. Women with identified osteoporosis following DXA scans will be informed of their exclusion from the trial as well as the rationale for exclusion and referred to their primary care physician. The trial inclusion and exclusion criteria are illustrated in Figure 4.

### 2.4. Interventions

All bacteria contained in the IP are commensal organisms that are known to inhabit the human gastrointestinal tract under normal conditions. Pendulum WBF-038 is a proprietary synbiotic formulation of five human-derived bacterial strains: *Akkermansia muciniphila* WB-STR-0001, *Anaerobutyricum* (formerly *Eubacterium*) *hallii* WB-STR-0008, *Clostridium butyricum* WB-STR-0006, *Clostridium beijerinckii* WB-STR-0005, and *Bifidobacterium infantis* Bi26TM, plus chicory inulin and magnesium stearate. The bacterial strains were grown in an FDA-registered food facility adhering to current good manufacturing practice conditions for food manufacturing facilities. Pendulum WBF-038 contains no genetically modified organisms, and its bacterial strains are generally recognized as safe.

The IP will be provided to the research team as acid-resistant capsules in identical bottles, which have been pre-coded by the supplier according to the randomization list and stored refrigerated at 4 °C. The participants received either Pendulum WBF-038 or matched placebo capsules containing only magnesium stearate. The daily dose in two capsules of WBF-038 is ≥2 × 10^9^ active fluorescent units. The dosage was determined in reference to a previous trial [71]. At T0, the participants will be dispensed IP along with calendars to record their adherence as well as a tip sheet on how to take the IP (Figures S1 and S2). The participants will be directed to take the assigned IP twice daily within 30 min of the morning and evening meals during phase 2 (treatment) of the trial. At six (T2), twelve (T4), and final (T5) visits, participants will be instructed to return the used IP containers (and any unconsumed IP), and compliance will be recorded. Compliance will be calculated based on returned capsules and the information recorded by participants on their IP calendars, with >80% compliance required for continuation in the study. The IP intake will be discussed at each visit to ensure compliance is tracking as per protocol. If a participant is unable to take the allocated IP because of an adverse event (AE), the researchers will alter the principal investigator according to internal guidelines.

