### 2.6. Visit Windows

The T0 visit date will set the follow-up visit dates, which will be booked one week on either side of the designated visit date unless there are extenuating circumstances (for example, unavailable due to illness). Any visit/contact that occurs outside one week on either side of the visit windows will be recorded in REDCap as a protocol deviation for that visit. Visits requiring blood sampling and stool collections will be conducted six months apart at T0, T2, and T4, with an additional stool collection at the final visit. Additionally, participants will be given a 72-h window in which to collect the stool samples and all materials required for the collection. Visits requiring fasted blood collection will be scheduled early in the morning and at a time convenient for study participants. The screen and T4 visits, which include DXA and HR-pQCT scans, will take no longer than 3 h to complete. Participants will be provided with breaks, food, and drinks at all in-person visits, as needed. To ensure adherence, participants will be sent email reminders of what a visit entails a week prior to each visit and contacted the day before the visit via telephone, where requirements for the visit will be discussed again.

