### 2.8. Sample Size

The sample size calculation was based on data from a previous probiotic intervention study in older women, which demonstrated a significant effect on bone health outcomes. For this study, additional metabolic outcomes are included, and effect sizes for these outcomes were estimated based on prior research using similar synbiotic interventions in comparable populations.

Permitting for possible participant attrition, the total sample size for the trial will be 160 (80 per arm), taking a 20–30% drop-out rate into account. Statistical power analysis will be performed in relation to the primary outcome of the relative twelve-month change (%) in total BMD using HR-pQCT at the distal tibia. On the basis of a similar probiotic intervention in older women [100], the expected decrease in tibia BMD is 1.85% in the placebo arm and 0.9% decline at most in the treatment arm, with a standard deviation (SD) of 1.6% and an alpha of 0.05; 46 participants are needed in each arm to achieve >80% power. To be able to detect smaller groups to group differences and to account for an attrition rate of 20–30% and due to many secondary outcomes, we will recruit a minimum of 80 participants into each arm.

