### 2.9. Statistical Analysis

All outcomes and analyses will be prospectively categorized as primary, secondary, or exploratory. Categorical variables will be described by numbers and percentages and 95% confidence intervals (CIs) for percentages based on a binomial distribution. Continuous variables will be described by means, SDs, medians, minima, and maximums, and 95% CIs for the means. The main comparisons will be of the intervention vs. placebo. With respect to dichotomous variables, Fisher’s exact test will be used to compare between the two groups. For continuous variables, Fisher’s nonparametric permutation test will be used.

To address the concern regarding multiple comparisons, the statistical analysis plan will include methods to control for Type I error across the primary and secondary outcomes. The primary variables will be investigated as the percentage difference from T0 to T4 visit between the two study groups. The trial will be deemed positive if the intervention vs. placebo is significant at the 0.05 significance level. The primary variable is anticipated to be normally distributed and analyzed by applying analysis of covariance (ANCOVA) with the relative change from T0 to T4 as the dependent variable, the treatment group as the fixed effect, and the T0 value as the covariate. The least square means with 95% CIs for the active treatment group vs. the placebo group will be presented together with the associated *p*-value.

The secondary variables are continuous and possibly will not be normally distributed. For secondary outcomes, adjustments will be made using appropriate correction methods, such as the Bonferroni adjustment for family-wise error control or the Benjamini–Hochberg procedure for controlling the false discovery rate, depending on the degree of correlation between outcomes. This approach ensures the integrity of the analyses while accounting for the diversity of outcomes assessed in the study.

Primary and secondary analyses will be conducted for the intention-to-treat as well as the per-protocol population. The difference in parameter estimates between the intervention and the placebo will be assessed for its clinical relevance. The secondary analyses will be considered exploratory, and an alpha of 0.05 will be applied with no further adjustments.

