Participants who supply both T0 and end-of-treatment samples will be included in a secondary dose–response analysis to account for early trial withdrawals or inadequate compliance.

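### The >80% compliance rule for staying in the study can remove randomised women before their only follow-up primary scan, selecting the intention-to-treat analysis towards adherers

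*Protocol article*

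**What the plan says.** Section 2.4 (Interventions) computes compliance from returned capsules and participants' calendars, "with >80% compliance required for continuation in the study". The condition is on continuing in the study, not on continuing the product or on entering an analysis set.

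On timing, the same section says: "At six (T2), twelve (T4), and final (T5) visits, participants will be instructed to return the used IP containers". Between counts, "The IP intake will be discussed at each visit to ensure compliance is tracking as per protocol".

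Section 2.6 (Visit Windows) places the primary measurement: "The screen and T4 visits, which include DXA and HR-pQCT scans". No other visit is given an HR-pQCT scan.

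Section 2.8 names the primary outcome as the "relative twelve-month change (%) in total BMD using HR-pQCT at the distal tibia". Section 2.9 analyses it by "analysis of covariance (ANCOVA) with the relative change from T0 to T4 as the dependent variable", and adds: "Primary and secondary analyses will be conducted for the intention-to-treat as well as the per-protocol population".

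Section 2.9 closes with a further analysis meant to deal with early withdrawal and poor compliance: "Participants who supply both T0 and end-of-treatment samples will be included in a secondary dose–response analysis".

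**The concern.** Compliance is observed after randomisation and may be related both to treatment and to bone loss. A rule that ends participation on that basis decides who can have a primary outcome. The intention-to-treat comparison is protected by randomisation only if women are followed whatever they take. Here the conduct rule may take out part of the group that separates an intention-to-treat set from a per-protocol set.

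Two things are at stake. If the share of women removed, or the kind of woman removed, differs between arms, the comparison is biased even when the product does nothing. If removal is equal and those removed are alike, there is no bias under the null, but the estimate describes women who comply rather than all who were randomised. A statistical analysis plan can define populations and impute values, but it cannot recover a scan that was never taken.

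**Working it through.** **Step 1: the plan's own figure.** Inputs from section 2.8: change of -1.85% on placebo and -0.9% on active, SD 1.6%, alpha 0.05 (sidedness not stated; two-sided assumed), 46 per arm for more than 80% power.

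- Difference = 1.85 - 0.9 = 0.95 points.
- Normal approximation: n = 2(1.96 + 0.84)² × 1.6² / 0.95², which rounds up to 45 per arm.
- Two-sample t-test: 45.5, rounded up to 46 per arm, power 80.4%.

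The figure of 46 reproduces. With 80 per arm and 20–30% dropout, 64–56 women per arm are scanned (power 91.5–87.6%). Loss can reach 1 - 46/80 = 42.5% per arm before the number falls below 46. Sample size is not the fault.

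**Step 2: when the rule can act, against when the outcome is measured.**

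| Visit | Compliance information | HR-pQCT |
|---|---|---|
| Screening | none | yes |
| T1, 3 months | intake discussed | no |
| T2, 6 months | capsules counted | no |
| T3, 9 months | intake discussed | no |
| T4, 12 months | capsules counted | yes |
| T5, 24 days after T4 | capsules counted | no |

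T2 is the only formal count before the T4 scan. A woman discontinued at T2, or after an intake discussion at T1 or T3, has no T4 value and cannot enter the ANCOVA without imputation. A woman whose low compliance is first counted at T4 is already at the scan visit.

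**Step 3: illustration when the product works.** Assumptions, none of them in the documents: a share m of the active arm is removed; if followed, these women would have lost bone at the placebo rate; 0.95 is the effect in those retained; women removed from placebo resemble the rest of that arm.

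All-randomised difference = 0.95 × (1 - m). Ratio of retained to all-randomised = 1/(1 - m).

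| m | All-randomised difference | Retained | Overstatement |
|---|---|---|---|
| 10% | 0.855 | 0.95 | 11% |
| 20% | 0.76 | 0.95 | 25% |
| 30% | 0.665 | 0.95 | 43% |

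Zero benefit is the unfavourable end. If removed women kept half the benefit (also assumed), the difference is 0.95 × (1 - 0.5m) = 0.90, 0.86 and 0.81, and the overstatement 1/(1 - 0.5m) - 1 = 5%, 11% and 18%.

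**Step 4: illustration when the product does nothing.** Assume 30% of each arm comply poorly and lose g = 0.5 to 1.0 points more bone, with 80 per arm and no other dropout. If shares p₁ (active) and p₀ (placebo) are removed, all of them poor compliers, the retained mean in each arm is shifted by -g(0.3 - p)/(1 - p).

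- p₁ = p₀ = 10%: false difference 0, type I error 5%.
- p₁ = 20%, p₀ = 10%: g × (0.2/0.9 - 0.1/0.8) = 0.097g, so 0.05–0.10 points; type I error 5.4–6.4%.
- p₁ = 30%, p₀ = 10%: g × (0.2/0.9 - 0) = 0.222g, so 0.11–0.22 points, or 12–23% of the planned 0.95; type I error 6.8–12.2%.

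**Step 5: internal consistency.** Section 2.4 says women at or below the threshold may not continue. Section 2.9 plans an analysis to account for inadequate compliance among women with end-of-treatment samples, which presumes that some of them do continue. The two statements need to be reconciled.

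**The case against.** The best defence is that the compliance clause is a one-line summary and was never meant to end follow-up. Planning separate intention-to-treat and per-protocol analyses, and a dose–response analysis for poor compliers, implies that some non-adherers will have data. Supplementary File S1 and the full protocol are not shown and may contain early-termination procedures. This tempers certainty about what happens in practice, but it does not remove the point. The dose–response analysis is secondary and concerns samples, not the primary scan. A closing scan at the time of removal would not give a twelve-month change. The clause as published still says study, not product.

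Four stronger readings are tempting, and the documents do not support them.

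- *The intention-to-treat set becomes an adherer set, almost identical to per-protocol.* Low compliance first counted at T4 can still be scanned, and per-protocol may exclude women for other reasons, such as prohibited probiotics or hormone therapy (section 2.5) or visit-window deviations (section 2.6).
- *The rule inflates the 20–30% attrition allowance.* Section 2.8 does not say whether that allowance already includes compliance removals.
- *Compliance will differ by arm.* Only the active capsules contain live strains and inulin, so a difference is possible, but no adherence or tolerability figures by arm are given and the capsules are matched.
- *The plan overstates the effect by 11–43%.* Those figures rest on assumed removal shares and on no benefit at all in a group that can include women taking 70–80% of their capsules.

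**Conclusion.** The concern holds in limited form. As written, the rule can remove randomised women, on a post-randomisation variable, before the only follow-up primary scan. The promised intention-to-treat estimate is then selected towards adherers, and sections 2.4 and 2.9 conflict.

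Bias requires that removal, or the type of woman removed, differ by arm. Without that, the estimate still describes compliers rather than everyone randomised. The size cannot be known from the documents. Under the assumptions in Step 3, the all-randomised difference would be 0.86–0.67 points against 0.95 in those retained. Under those in Step 4, unequal removal produces a false difference of 0.05–0.22 points.

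Power is a minor matter; the harm is to what the primary analysis means. It deserves correction now because the trial is under way and each missed T4 scan is lost for good.

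**What to change.** Reconcile sections 2.4 and 2.9 with wording to this effect: low compliance does not end study participation; the T4 HR-pQCT and all other T4 assessments are sought in every randomised participant whatever her product intake; compliance above 80% defines only membership of the per-protocol set. Any rule on product use should be stated separately from the follow-up rule; this point takes no position on what that rule should be.

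Because the trial has started, invite women already discontinued for low compliance to T4 where possible, and report how many there were in each arm, with the timing of their removal.

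The cost is a short amendment, some further T4 visits, and possibly a smaller intention-to-treat effect. That smaller effect would be the answer to the question the trial says it is asking. Women whose T4 date has already passed cannot be recovered by the amendment, which is why their number by arm should be reported.
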